## Abstract

Progressive resistance exercise training (PRET) reduces cardiovascular risk factors (CVRF) in the general population. It is unknown if PRET also reduces these risk factors in adults with intellectual disabilities (ID). The aim is to present the protocol of an intervention study that investigates the effect of PRET on CVRF in adults with ID. We will use a repeated time series design with one study group. Adults with mild-to-moderate ID and at least two CVRF are eligible (Netherlands Trial Register, NL8382). During a 12-week baseline period, measurements take place at a 6-week interval. After this, the PRET programme starts for 24 weeks, after which all measurements will be repeated. We will use hierarchical regression models, adjusted for sport activity and medication use, to estimate the effect of PRET. After the intervention, the participants will be followed-up for 12 weeks. We will evaluate factors for successful implementation of exercise in daily life. Primary outcomes are: hypertension, obesity, hypercholesterolemia, diabetes, metabolic syndrome. Secondary outcomes are: physical fitness, sarcopenia, physical activity, activities of daily living, falls, challenging behaviour. If our results show that the PRET programme is effective, it may be a promising non-pharmacological intervention to reduce CVRF in adults with ID.

## 1. Introduction

The life expectancy of people with intellectual disabilities (ID) is increasing and approaching that of the general population [1,2]. However, an increased life expectancy does not mean that people with ID are ageing healthy. The Healthy Ageing and Intellectual Disabilities (HA-ID) study found that cardiovascular risk factors (CVRF) were highly prevalent in adults with ID of 50 years and over. Hypertension was seen in 53% of the participants, obesity in 46–48%, hypercholesterolemia in 23%, diabetes in 13%, and metabolic syndrome in 45% [3].

When CVRF are present, it is recommended to use either medication or promotion of a healthy lifestyle to prevent the development of cardiovascular disease [4]. Because adults with ID are more likely to be exposed to polypharmacy [5], promoting a healthy lifestyle and physical activity may have an even more important role in reducing cardiovascular risk. Unfortunately, most adults with ID have an inactive lifestyle with only 9% of them achieving physical activity levels needed for gaining health benefits [6].

Resistance exercise training is a well-studied intervention that reduces CVRF in the general population [7,8,9,10] and may be promising to reduce CVRF in adults with ID as well. For adults with cardiovascular and metabolic disease, the American College of Sports Medicine (ACSM) guidelines recommend a progressive resistance exercise training (PRET) programme at vigorous intensity for all large muscle groups [11]. Although research has been conducted in the general population, it is still unknown whether PRET is beneficial for reducing CVRF in adults with ID. Studies indicate that the physiological responses to exercise are different in people with ID. For example, there are indicators that during exercise they have a blunted blood pressure and baroreflex sensitivity response [12,13], and a lower maximal heart rate and peak oxygen uptake [14] than people in the general population. Therefore, the effect of exercise interventions may differ for this population, and we cannot generalize the results from the general population to people with ID.

Due to low physical activity levels [15], adults with ID are prone to other health problems. Low levels of physical activity can result in loss of muscle strength and muscle mass which can lead to sarcopenia at older age [16]. Sarcopenia is characterised by progressive and generalised loss of skeletal muscle mass and strength with a risk of adverse health outcomes [17]. Sarcopenia has been found prevalent in older people with ID, at already younger ages than in the general population [17,18]. In the general population resistance training reduces sarcopenia [19], as it increases the muscle strength and muscle mass [20]. Other studies showed that people with ID have poor balance, strength, muscular endurance, and gait speed [15,21] which can lead to difficulties in performing activities of daily living and thereby increase the dependency of caregivers [22] and falls. In addition to these health problems, challenging behaviour, such as aggression and self-injury, is common [23]. Team sports seem to reduce challenging behaviour [24], but it is still unknown if resistance training is effective in reducing challenging behaviour in adults with ID.

A PRET programme may enhance physical activity and be beneficial for people’s cardiovascular risk profile and health in general. In a previous study, we composed a Resistance Exercise Set for adults with ID (RESID) [25]. We found that these exercises were feasible to perform by adults with mild to moderate ID and CVRF [26]. Therefore, the RESID can be used in the PRET programme as the content of the training sessions. This programme may be an additional intervention to existing pharmacological treatments for CVRF in adults with ID. To our knowledge, no study investigated the effect of PRET on reducing the above-described health issues in this population. The primary aim of this study is to investigate the effect of the PRET programme on CVRF (hypertension, obesity, hypercholesterolemia, diabetes, and metabolic syndrome) in adults with ID. Second, we will investigate the effect of PRET on physical fitness, sarcopenia, physical activity, activities of daily living, falls, and challenging behaviour. This paper presents the study protocol, outcomes, and statistical analysis plan.

## 2. Material and Methods

### 2.1. Study Design

This study has a repeated time series design with one study group. The study period will last one year and is divided into a 12-week baseline period, a 24-week intervention period (PRET programme), and a 12-week follow-up period. We will use the baseline measurements for control comparisons.

This study follows the principles of the Declaration of Helsinki [27] and is in accordance with the Dutch Medical Research Involving Human Subjects Act. We obtained ethical approval from the Medical Ethical Committee of the Erasmus MC, University Medical Center Rotterdam in the Netherlands (MEC-2019-0544). The study is registered in the Netherlands Trial Register (NTR, NL8382). Written informed consent will be obtained from all participants or their legal representatives.

### 2.2. Study Population, Recruitment, and Inclusion

This study will be conducted within the Healthy Ageing and Intellectual Disability (HA-ID) consortium. The HA-ID consortium is a collaboration between the Chair of Intellectual Disability Medicine of the Erasmus MC, University Medical Center Rotterdam and three care providers in the Netherlands specialised in care for people with ID: Ipse de Bruggen (Zoetermeer), Abrona (Huis ter Heide), and Amarant (Tilburg).

Figure 1 summarises the inclusion and exclusion criteria for this study. Participants must meet the following criteria to be included: (1) being 18 years or older; (2) living in a residential facility or receiving care from one of the participating care providers; (3) diagnosed with mild (IQ = 50–69) or moderate (IQ = 35–49) ID [28]; (4) diagnosed with metabolic syndrome [29], or at least two of the following CVRF: hypertension [30], hypercholesterolemia [4], diabetes mellitus type 2 [31], or obesity [32]. Metabolic syndrome is defined as the presence of any three of the following CVRF: elevated waist circumference, elevated blood pressure, elevated fasting glucose, elevated triglycerides, and low high density lipoprotein cholesterol [29]. Cut-off values for the CVRF are summarised in Table 1. Furthermore, participants must be able to walk independently and able to follow instructions on posture and performance for good execution of the exercises.

We will develop a query to screen medical files for potential participants. Potential participants are screened by a physical therapist for their eligibility and expected adherence to the PRET programme. To identify health issues that make participation in the PRET programme unsafe, the professional caregiver of eligible participants will fill out the Physical Activity Readiness Questionnaire (PAR-Q) [33]. If a positive response to any of the items of the PAR-Q is given, the participant’s physician will do a health check to assure safe participation. Participants who do not obtain medical clearance from their physician or have physical limitations (including neurological and orthopaedic conditions) interfering with participation in the PRET programme will be excluded from the study.

### 2.3. Informed Consent Procedure

All potential participants will receive study information and a consent form. A behavioural scientist will assess if potential participants understand the easy-read study information and if they are able to decide for participation themselves. If potential participants are not able to make an informed decision, we will also send the study information and a second consent form to their legal representative and ask them for a decision.

### 2.4. Intervention

The PRET programme will take 24 weeks and consists of two sessions per week, with at least 48 h between the sessions. The intervention will be led by experienced physiotherapists and physical activity instructors employed by the care providers. All instructors take part in a training prior to the study. In this training, the intervention protocol and exercises will be discussed and practiced ensuring that the intervention is delivered according to the protocol. Every session consists of seven exercises (RESID) to train all large muscle groups [25]. For each muscle group, alternative exercises will be provided for participants who are not able to perform the original exercise with a correct execution. The instructor-participant ratio will be 1 to 1 or 1 to 2.

Table 2 summarises the training parameters of the PRET programme. The programme is in accordance with the ACSM guidelines [11] and characterised by four mesocycles. Each mesocycle consists of six weeks of training. After each mesocycle the training intensity will increase gradually, and within each mesocycle the weights will be adjusted in a way that the intensity remains equal. Training intensity will be measured by the percentage of the heaviest load one can lift for one repetition (% of 1RM) [34]. In the first mesocycle, participants are introduced to the resistance exercises and familiarised to the training protocol. They will learn to perform the exercises safely and with good posture. During mesocycles 2, 3, and 4, the number of repetitions will be gradually decreased while the training intensity will be gradually increased until vigorous intensity is reached in the fourth mesocycle (80% of 1RM). The resting time between sets will depend on the training intensity and varies between 30 s and 2 min.

The instructors will register attendance, training intensity, performed number of sets and repetitions, and the weights used for each exercise in a log. To maximise attendance and motivation, each participant receives a progression certificate to track their progress and a T-shirt to wear during the training and measurements. At completion of the programme, the participant receives a certificate and a medal.

### 2.5. Co-Interventions

Participants will continue their usual activities but cannot start another intervention or activity to improve their physical activity level during the study period. Medical interventions that are necessary for regular care are allowed to start. All changes in sport activities and medication use related to CVRF will be recorded.

### 2.6. Primary Outcomes

The following CVRF are the primary outcomes.

#### 2.6.1. Hypertension, Blood Pressure

A trained researcher will use the Omron-M7 (Omron Healthcare, Kyoto, Japan) to measure blood pressure from both arms after sitting for two minutes without talking. The Omron-M7 has been found valid according to the international protocol of the European Society of Hypertension [35]. We will select the arm with the highest value for the actual measurement. This arm will be measured twice, and the average score (mm/Hg) for systolic (SBP) and diastolic (DBP) blood pressure will be recorded. Participants will be classified as hypertensive if SBP ≥ 140mm/Hg, and/or DBP ≥ 90mm/Hg [30]. If the automated blood pressure measurement repeatedly fails, for example when the reading is distorted by movement of the cuff, we will use a sphygmomanometer to manually measure the participants’ blood pressure.

#### 2.6.2. Obesity, Waist, and Hip Circumference

A trained researcher will use a measuring tape (Seca 200, Seca, Hamburg, Germany) to measure waist and hip circumference [32]. Waist circumference will be measured at the midpoint between the lowest palpable rib and the top of the iliac crest. Hip circumference will be measured around the widest portion of the buttocks. Each measurement will be repeated twice. If the repeated measurements are within 1cm of one another, we will calculate an average score (cm). If the difference between the measurements exceeds 1cm, the two measurements will be repeated [32]. Male participants will be classified as obese if their waist circumference >94 cm and their hip-waist ratio ≥0.90, and female participants if their waist circumference >80 cm and their hip-waist ratio ≥0.85 [32].

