## Figures and Tables

**Figure 1 ijerph-19-16438-f001:**
[figure not shown]
Study recruitment and procedures. ACSM: American College of Sports Medicine; CVRF: cardiovascular risk factors; ID: intellectual disability IQ: intelligence quotient.

**Table 1 ijerph-19-16438-t001:** Definitions of cardiovascular risk factors (CVRF).

Cardiovascular Risk Factor	Reference	Markers	Values
Metabolic syndrome, having 3 out of 5 markers	Alberti et al. (2009) [29]	Waist circumference	≥94 cm (men) * ≥80 cm (women) *
		Fasting glucose (FG)	>5.6 mmol/L
		High density lipoprotein (HDL-C)	<1 mmol/L (men) <1.3 mmol/L (women)
		Triglycerides (TG)	>1.7 mmol/L
		Systolic blood pressure (SBP) and diastolic blood pressure (DBP)	≥130 mm/Hg and ≥85 mm/Hg
Hypertension (Stage 2)	Whelton et al. (2017) [30]	Systolic blood pressure (SBP)	≥140 mm/Hg
		Diastolic blood pressure (DBP)	≥90 mm/Hg
Hypercholesterolemia	Piepoli et al. (2016) [4]	Total cholesterol (TC)	>4 mmol/L
		Low density lipoprotein (LDL-C)	≥2.6 mmol/L
Diabetes mellitus type 2	American Diabetes Association (2018) [31]	Fasting glucose (FG)	≥7 mmol/L
		HbA1c	≥48 mmol/L
Obesity	World Health Organisation (2008) [32]	Waist Circumference	>94 cm (men) * >80 cm (women) *
		Waist-hip ratio	≥0.90 (men) ≥0.85 (women)

* European, Caucasian threshold, mm/Hg: millimetres of mercury; mmol/L: millimoles per litre.

**Table 2 ijerph-19-16438-t002:** Training parameters according to the ACSM guidelines [11].

Mesocycle	% of 1RM	Number of Sets	Number of Repetitions	Rest between Sets
1	-	1–2	20	30 s
2	65	2	15	1 min
3	75	3	10	1 min
4	80	3	8	2 min

ACSM: American College of Sports Medicine; 1RM: one-repetition maximum.

**Table 3 ijerph-19-16438-t003:** Classification for Sarcopenia cut-off [17].

Domain	Tests	Values
*Sarcopenia*		
Muscle strength	Five times chair stand	>15 s for 5 rises
	Grip strength	<27 kg (men) <16 kg (women)
Muscle mass	BIA	<20 kg (men) <15 kg (women)
*Severe sarcopenia*		
Muscle strength	Five times chair stand	>15 s for 5 rises
	Grip strength	<27 kg (men) <16 kg (women)
Muscle mass	BIA	<20 kg (men) <15 kg (women)
Physical performance	Gait speed	≤0.8 m/s

BIA: bioelectrical impedance analysis; kg: kilogram; m/s: meter per second.

**Table 4 ijerph-19-16438-t004:** Items and adapted scoring based on Lawton and Brody IADL.

Items Lawton and Brody IADL [43]	Items derived from GARS [45]	Items and Adapted Scoring Used in This Study
*Items*		
Using the telephone		Using the telephone
Shopping		Shopping

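### The ratio in the section 2.6.2 obesity definition is the reciprocal of the one in Table 1, so read literally it barely restricts the waist criterion

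*Protocol article*

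**What the plan says.** The abstract lists obesity among the primary outcomes: "Primary outcomes are: hypertension, obesity, hypercholesterolemia, diabetes, metabolic syndrome".

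Section 2.6.2 gives the classification rule. For men: "Male participants will be classified as obese if their waist circumference >94 cm and their hip-waist ratio ≥0.90". For women: "female participants if their waist circumference >80 cm and their hip-waist ratio ≥0.85". Both parts of the rule must be met, and reference 32 is cited.

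The obesity row of Table 1 cites the same reference and gives the same waist limits (above 94 cm for men, above 80 cm for women) and the same ratio cut-offs (0.90 and 0.85). It names the ratio "Waist-hip ratio".

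For eligibility, section 2.2 sends the reader to the table: "Cut-off values for the CVRF are summarised in Table 1".

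Section 2.11.2 plans hierarchical linear and logistic regression over T0 to T3. A yes/no obesity classification would go into the logistic model.

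**The concern.** Hip divided by waist is the reciprocal of waist divided by hip. Attaching the same lower limit to both cannot give the same rule. In Table 1 the ratio sets a floor on central fat distribution. In section 2.6.2, taken literally, it sets a ceiling. The reversed term appears twice in the sentence, once for each sex, so it is not an artefact of text extraction.

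Section 2.6.2 is where an analyst would look for the rule that classifies this primary outcome. Coding it as written changes who counts as obese at each visit, and so changes the data in the logistic model. The error might not show in the output, because the resulting prevalence would look plausible: close to that from waist circumference alone.

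**Working it through.** The plan gives no figure to reproduce here. The check is algebra, worked examples, and a calculation under stated assumptions.

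**Inputs from the documents.** Waist limits 94 and 80 cm; ratio cut-offs c = 0.90 (men) and 0.85 (women); hip-waist in section 2.6.2, waist-hip in Table 1.

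**Inversion.** Hip/waist ≥ c is the same condition as waist/hip ≤ 1/c.
- Men: 1/0.90 = 1.111
- Women: 1/0.85 = 1.176

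Among people over the waist limit, the two rules agree only when waist/hip lies between c and 1/c. Below c, the text says obese and Table 1 does not. Above 1/c, Table 1 says obese and the text does not.

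**Examples (illustrative measurements).**

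| Person | Waist / hip (cm) | Waist/hip | Hip/waist | Table 1 | Section 2.6.2 |
|---|---|---|---|---|---|
| Man | 100 / 105 | 0.95 | 1.05 | obese | obese |
| Man | 95 / 110 | 0.86 | 1.16 | not obese | obese |
| Man | 115 / 100 | 1.15 | 0.87 | obese | not obese |
| Man | 85 / 105 | 0.81 | 1.24 | not obese | not obese |
| Woman | 85 / 105 | 0.81 | 1.24 | not obese | obese |

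**Change over time, hip held constant.**
- Man, hip 100, waist 115 to 110: hip/waist goes from 0.87 to 0.91. The text moves him from not obese to obese; Table 1 keeps him obese (1.15 to 1.10).
- Woman, hip 106, waist 92 to 89: waist/hip goes from 0.87 to 0.84. Table 1 records a change to not obese; the text records no change (hip/waist 1.15 to 1.19).

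**Share classified differently.** The documents give no waist-hip distribution. Assume that, among those over the waist limit, waist/hip is normal with mean m and SD 0.07. Then

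added by the text = Φ((c − m)/0.07); dropped by the text = 1 − Φ((1/c − m)/0.07).

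For men at m = 0.92: Φ(−0.286) = 38.7% added, and 1 − Φ(2.730) = 0.3% dropped.

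| Sex | Assumed mean | Added | Dropped | Total |
|---|---|---|---|---|
| Men | 0.92 | 38.7% | 0.3% | 39.1% |
| Men | 0.96 | 19.6% | 1.5% | 21.1% |
| Men | 1.00 | 7.7% | 5.6% | 13.3% |
| Men | 1.04 | 2.3% | 15.5% | 17.8% |
| Women | 0.82 | 66.6% | <0.1% | 66.6% |
| Women | 0.86 | 44.3% | <0.1% | 44.3% |
| Women | 0.90 | 23.8% | <0.1% | 23.8% |
| Women | 0.94 | 9.9% | <0.1% | 10.0% |

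Totals are rounded from unrounded parts. A separate simulation also drew waist (men mean 105, SD 13; women mean 100, SD 14; all assumed) and counted everyone, including those under the limit. With mean ratios of 0.90-1.05 for men and 0.80-0.95 for women, it gave disagreement of about 11-40% and 7-70%. In women the literal rule classified 92% as obese, the same as waist alone. In men it gave 80% against 80% at mean ratio 0.90, and 65% against 80% at mean ratio 1.05.

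**The case against.** The strongest reply is that this is a transposed word. The cut-offs, waist limits and reference are identical in both places, and Table 1 is the table of definitions, so the intended ratio is easy to infer. Waist and hip are measured separately in centimetres, so the correct ratio can be computed at any time and no data are lost. The sample size in section 2.12 rests on HbA1c and is untouched. All of this stands. It makes the repair easy, but it leaves a wrong rule in the section that defines the outcome.

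A reader might go further and infer that the obesity outcome runs backwards, that it cannot change in women, or that the wrong people will be enrolled. The documents do not support these readings:
- The rule joins two conditions, and the waist condition runs in the right direction. Anyone whose waist falls to the limit or below becomes non-obese under either rule, so a woman can still change status by crossing 80 cm.
- True reversal needs a waist/hip above 1.11 (men) or 1.18 (women) with the waist still over the limit. Under the assumptions above this is negligible in women, and in men it is the larger part of the disagreement only at the highest mean.
- Section 2.2 refers eligibility to Table 1, which has the waist-hip wording. Nothing shown indicates that the screening query or any code uses hip/waist.

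**Conclusion.** The contradiction is certain and can be seen from the article alone: section 2.6.2 and Table 1 attach the same cut-offs to reciprocal ratios. Read literally, the ratio condition in section 2.6.2 is reversed. Its main practical effect is that it hardly restricts the waist criterion. In women it amounts to waist circumference alone. In men it is close to that unless the mean waist-hip ratio is high, when it also removes the most centrally obese.

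The number of participants affected is uncertain. The range of roughly 10-40% of men and 10-70% of women over the waist limit rests on an assumed normal distribution, an assumed SD of 0.07 and assumed means. It shows that the rules can differ materially, not by how much they will differ in this sample. The error also matters only if the outcome is coded from the text rather than from Table 1. Because it concerns the definition of a primary outcome and costs almost nothing to correct, it should be corrected before the analysis.

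**What to change.** In section 2.6.2, replace the hip-waist term with waist-hip ratio (waist divided by hip) for both men and women, so that it matches Table 1. Leave the cut-offs and waist limits as they are. Confirm that the code classifying the obesity outcome divides waist by hip. The cost is one line of text and one code check. No new measurements are needed, and the sample size does not change.

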#### 2.6.3. Hypercholesterolemia, Diabetes, and Metabolic Syndrome

The medical staff of the care providers will collect blood samples after overnight fasting. The samples will be analysed at the laboratory of the Erasmus MC. We will measure total cholesterol (TC), low-density lipoprotein (LDL-C), high-density lipoprotein (HDL-C), triglycerides (TG), HbA1c and fasting glucose (FG) in mmol/L. Participants will be classified as having hypercholesterolemia when TC > 4 mmol/L and LDL-C ≥ 2.6 mmol/L [4]. Cut-of values for classifying participants as having diabetes mellitus type 2 are set at ≥48 mmol/L for HbA1c and ≥7 mmol/L for FG [31]. Participants will be classified as having metabolic syndrome when at least three of the following CVRF are present: elevated waist circumference (≥94 cm for men, ≥80 cm for women), elevated blood pressure (SBP ≥ 130 mm/Hg, and/or DBP ≥ 85 mm/Hg), elevated FG (>5.6 mmol/L), elevated triglycerides (>1.7 mmol/L), and low HDL-C (<1 mmol/L for men, < 1.3 mmol/L for women) [29].

